### Sample size considerations

A power analysis conducted a priori using G*Power was based on the results of a meta-analysis that reported a moderate to large effect size of Cohen’s *d* = 0.64 [16] for between-group differences in maternal sensitivity. Assuming a two-sided α of 0.05 and the computation of an analysis of covariance (ANCOVA) model with maternal sensitivity at 6 weeks as the dependent variable, and maternal sensitivity at baseline as a covariate, this resulted in a required sample size of *n* = 64 (per group) with a power of 90%. Assuming a drop-out rate of 20% [14], the sample size calculates to *n* = 80 per group (total sample size *N* = 160 mother-child dyads). This sample size will also enable the detection of interaction effects considering a moderate moderator effect in the ANCOVA (corresponding to an effect size of *d* = 0.44) with a power of 80%. We initially planned to recruit a sample of 180 infants with a diagnosis of a regulatory disorder and their mothers. However, difficulties in recruitment and funding period constraints meant the planned sample size was reduced to *N* = 160 in June 2020.

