### Trial design

The two-armed, open, randomised, controlled multicentre study with parallel groups and blinded endpoint assessment (PROBE design; prospective randomised, blinded endpoint) with a six-week intervention is currently underway in Leipzig, Berlin, Potsdam and Hamburg. All study centres and participating clinics there provide focused and supervised certified PIP in accordance with a previously elaborated SKKIPPI Study Manual ([name], [name], [name]: SKKIPPI Study manual for Parent-Infant-Toddler Psychotherapy (PIP), Unpublished). Depending on the severity of the child’s pathological symptoms, and in agreement with parental preferences, a decision is made on treatment setting (in−/outpatient) before randomisation. Participants are then randomly assigned to either PIP or CAU, and data are collected at three measurement points: at baseline before intervention, immediately after treatment, and at 12 months follow-up. The biostatistician of the Institute for Social Medicine, Epidemiology, and Health Economics at the Charité – Universitätsmedizin Berlin generates the allocation sequence based on a computer generated random list, applying a 1:1 block randomisation with variable block length and stratified by setting (inpatient/outpatient) and study centre. Mother-child dyads are randomly assigned to either PIP or CAU.

Before being enrolled in the trial, participants are screened by a professional physician or psychotherapist for eligibility and clinical diagnoses. Only children receiving an ICD-10 diagnosis of regulatory disorder can take part in the study. Eligible mothers of these children are informed verbally about the study, and written informed consent must be given before randomisation. Afterwards, baseline assessments are carried out, and the 6 weeks of interventions start. At the end of treatment, participants are assessed again, as well as 12 months after baseline. Mothers will receive €100 as monetary compensation (25€ after Baseline, 25€ after 6 weeks follow-up and 50€ after the last assessment) until the 12-months follow-up. Throughout the study, the study nurse is in contact with the participants via phone calls or e-mails to schedule appointments. Treatment allocation is masked to the assigning personnel and there are no special criteria for discontinuing or modifying the allocated intervention (Fig. 1).

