#### Primary endpoint

The primary analysis of the primary endpoint (maternal sensitivity measured using the EAS subscale after 6 weeks) will be analysed using ANCOVA based on the FAS population using PIP versus CAU as the factor treatment group, EAS sensitivity at baseline as covariate, and the stratification variable treatment setting. Results will be displayed as adjusted means of the treatment group together with 95% confidence intervals and the respective *p* value (two-sided). The significance level is set at α =0.05. All further analysis is considered exploratory.

A secondary analysis of the primary endpoint will also be carried out using the ANCOVA model based on the PP population. Additional moderator analyses of the efficacy of PIP for a change in maternal sensitivity (EAS) will be conducted with treatment setting as the moderator, i.e. by additionally adding a ‘treatment group’ * ‘treatment setting’ interaction term to the model. Further moderator analyses regarding the efficacy of PIP will comprise maternal attachment type (AAI attachment) or maternal reflective functioning (AAI RF) as moderators.

In addition, models incorporating multiple imputation methods based on the PP population and a hierarchical regression model (including the therapist as a grouping factor and therapist’s adherence as covariate) will be used for sensitivity analyses of the primary outcome. To investigate the longitudinal change of the primary endpoint, linear mixed models (LMMs) incorporating both measurement points for each outcome (FAS population) will be computed. To explore further effects of additional predictors (such as the therapists carrying out the interventions), the models will be compared based on model fit values (AIC, the Akaike Information Criterion), with these predictors included in the model term.

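### The stated sample size, power and effect size do not agree: d = 0.64 at 90% power needs 53 evaluable dyads per group, not 64, and 64 per group gives about 95% power

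*Protocol article*

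**What the plan says.** Sample size considerations presents one derivation, run in G*Power. The target is a standardised between-group difference of d = 0.64 in maternal sensitivity, taken from a cited meta-analysis. The error rate is given as "Assuming a two-sided α of 0.05". The model is an ANCOVA with "maternal sensitivity at 6 weeks as the dependent variable, and maternal sensitivity at baseline as a covariate". From these inputs, the article says, "this resulted in a required sample size of *n* = 64 (per group) with a power of 90" per cent. Drop-out is then added: "Assuming a drop-out rate of 20% [14], the sample size calculates to *n* = 80 per group", for a total of 160 dyads.

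Two other sections settle what the calculation has to assume. The Primary endpoint section defines the model as "using PIP versus CAU as the factor treatment group, EAS sensitivity at baseline as covariate, and the stratification variable treatment setting", so treatment has two levels. The Trial design section describes allocation as "applying a 1:1 block randomisation with variable block length", so the arms are equal.

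**The concern.** Effect size, significance level, power, model and allocation are all printed, so the required number can be checked directly. Any three of effect, alpha, power and n fix the fourth, and here the four do not match. A standardised difference of 0.64 is fairly large, and 64 per group is noticeably more than 90% power calls for.

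This is not a matter of detail that an article may leave to a fuller protocol or analysis plan. The article gives the inputs and the result together as a single derivation, and the result does not follow. It is also the power statement for the only confirmatory test, since the Primary endpoint section treats all further analysis as exploratory. Anyone who uses it later to judge what a null result excludes, or who repeats it in the results paper, would carry a wrong figure forward.

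**Working it through.** **Inputs.** d = 0.64, two-sided alpha 0.05, power 90%, stated n = 64 per group, ANCOVA with baseline covariate, drop-out 20% (all from Sample size considerations); two treatment levels, hence 1 numerator df (Primary endpoint); 1:1 allocation (Trial design). The effect is standardised, so SD = 1. No baseline–outcome correlation and no clustering allowance are stated.

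**1. Normal approximation.** n per group = 2(z₀.₉₇₅ + z₀.₉₀)² / d² = 2(1.960 + 1.282)² / 0.64² = 2 × 10.51 / 0.4096 = 51.3, so 52.

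**2. Exact t test.** Noncentrality = d√(n/2), with 2n − 2 df.

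| n per group | noncentrality | power |
|---|---|---|
| 52 | 0.64 × √26 = 3.26 | 89.8% |
| 53 | 0.64 × √26.5 = 3.29 | 90.4% |
| 64 | 0.64 × √32 = 3.62 | 94.9% |

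**3. ANCOVA F test of the G*Power type.** f = d/2 = 0.32, noncentrality = f²N, 1 numerator df.
- The smallest N for 90% power is 105 (0.1024 × 105 = 10.75), that is 53 per group with equal arms.
- At N = 128 (0.1024 × 128 = 13.11) the power is 94.9%.
- N = 105 is unchanged with 2, 4 or 8 cells and with one or two covariates, so adding treatment setting to the model does not explain the difference.

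**4. Reproducing the plan's own figure.** The figure of 64 at 90% is not reproduced. The gap is 64 − 53 = 11 per group, and 11/53 = 21%. The drop-out step is correct: 64 / 0.80 = 80. Starting from 53 it would give 53 / 0.80 = 66.25, so 67 per group.

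**5. Do variants of the stated inputs close the gap?**
- A one-sided test gives 43 per group.
- Crediting a baseline–outcome correlation r (assumed values, since none is stated) replaces the variance by 1 − r² and lowers n. By the normal formula it is 47, 39 and 27 per group at r = 0.3, 0.5 and 0.7.

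Both move away from 64.

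**6. Settings outside the stated inputs that land at or near 64.**
- Power of 95%: 2(1.960 + 1.645)² / 0.4096 = 63.5, so 64 by the normal formula; 65 by the exact t.
- Two numerator df: N = 127, so 64 per group, but this does not fit a two-arm contrast.
- An effect of about 0.58 at 90% power.
- 53 × 1.20 = 63.6, which would count drop-out twice.

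The article does not show which of these, if any, occurred.

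**7. What 64 evaluable dyads per group do provide.** Detectable d is 0.577 at 90% power and 0.499 at 80% power.

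**The case against.** The best defence is that the error is harmless. The stated n exceeds what the stated effect needs, so the primary test is better powered at d = 0.64 than claimed, and enrolment, alpha and model are untouched. That stands, and it limits the point to a correction of text.

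A second defence is that the extra dyads may be an unstated allowance for therapist clustering, since the Primary endpoint section uses therapist as a grouping factor in a sensitivity analysis. An inflation of 64/53 = 1.21 would bridge the gap. This is an assumption with nothing in the sample size section behind it, so it does not rescue the sentence. It does mean that a flat claim of 95% power should say that clustering is ignored.

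A reader might also infer several stronger things that the article does not support.
- **That a calculation ending at 160 cannot lie behind the original plan.** The article says "We initially planned to recruit a sample of 180 infants with a diagnosis of a regulatory disorder and their mothers" and gives no basis for that number. Recruitment may have been set above a calculated minimum, or with more drop-out in mind: 64 evaluable out of 90 per group is a loss of about 29%.
- **That power was used to defend the cut to 160.** The article attributes the cut to recruitment and funding. Power would in any case have changed little: 180 × 0.8 / 2 = 72 per group gives 96.8%, against 94.9% at 64.
- **That the target effect cannot be identified.** It is stated plainly as d = 0.64, with its source. What is unclear is the setting that turned it into 64.
- **That 80 − 67 = 13 dyads per arm are surplus.** The article gives N = 160 a second purpose, an interaction of d = 0.44 at 80% power. A 1-df F test (f = 0.22) gives 79.0% at N = 160 and about 69% at 128 evaluable dyads, so the total is not plainly in excess.

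**Conclusion.** The point holds as an inconsistency among printed figures. With d = 0.64, two-sided 5%, two equal arms and 1 numerator df, 90% power needs 53 evaluable dyads per group, and 64 per group gives about 95%. The required number is overstated by 11 per group, or the power understated by about 5 percentage points. The exact t and the ANCOVA F test agree on this.

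The result assumes independent dyads and takes no credit for the baseline covariate. Crediting the covariate would widen the gap; a clustering allowance would narrow it, but none is stated. The error is conservative and leaves the primary test adequately powered at the stated effect. The origin of 64 cannot be determined from the article, so no particular mistake should be attributed to the sponsor.

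**What to change.** Keep N = 160 and replace the power sentence along these lines:

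> With 64 evaluable dyads per group, power is about 95% for d = 0.64, 90% for d = 0.58 and 80% for d = 0.50 (two-sided 5%, no credit for baseline adjustment, ignoring therapist clustering).

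If the G*Power run used an input other than those printed (effect size, numerator df, target power or an inflation factor), state that input and correct the sentence to match it. The numerator df and number of groups entered should be given in either case.

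The cost is a text correction. Enrolment, randomisation, the analysis model and the significance level stay as they are.

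### The stated 80% power for a moderator effect of d = 0.44 needs all 160 randomised dyads; at the planned 128 evaluable it is about 70%, and for treatment by setting that effect is a 0.88 SD difference, not a moderate one

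*Protocol article*

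**What the plan says.** Under *Sample size considerations*, the protocol article takes a meta-analysis that "reported a moderate to large effect size of Cohen’s *d* = 0.64" for maternal sensitivity. It assumes a two-sided α of 0.05 and an ANCOVA with baseline sensitivity as covariate, and reports that "this resulted in a required sample size of *n* = 64 (per group) with a power of 90" per cent. It then allows for attrition: "Assuming a drop-out rate of 20% [14], the sample size calculates to *n* = 80 per group (total sample size *N* = 160 mother-child dyads"). The next sentence extends the claim to moderators: "This sample size will also enable the detection of interaction effects considering a moderate moderator effect in the ANCOVA", the effect being described as "corresponding to an effect size of *d* = 0.44) with a power of 80" per cent.

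Under *Primary endpoint*, the first moderator named is setting: "Additional moderator analyses of the efficacy of PIP for a change in maternal sensitivity (EAS) will be conducted with treatment setting as the moderator". This is done by adding a treatment-by-setting product term to the primary model. Maternal attachment type and reflective functioning are listed as further moderators. The same section makes everything beyond the primary analysis exploratory. Under *Missing data*, the primary analyses are run without imputing missing values.

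**The concern.** Two things look wrong. First, the main effect is sized on 64 evaluable dyads per group, but the moderator sentence, directly after the drop-out allowance, refers to the full inflated sample. A dyad without a 6-week sensitivity score contributes nothing to an ANCOVA run without imputation, so the two power statements rest on different sample sizes.

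Second, d is a difference between two means, whereas an interaction with setting is a difference between two such differences. The text does not say what d = 0.44 means on that scale. A reader will probably take it as the benefit of PIP differing by 0.44 SD between inpatient and outpatient care, which is not what the power figure covers.

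The *Discussion* presents the study of PIP in different settings as the trial's main strength. A design-stage claim of 80% power would make a null interaction look more informative than it can be.

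**Working it through.** **Inputs from the protocol article**
- α = 0.05, two-sided; interaction effect d = 0.44; stated power 80%; main effect d = 0.64 (*Sample size considerations*).
- Randomised N = 160. Evaluable N = 160 × (1 − 0.20) = 128, which is 2 × 64 (same section).
- 1:1 allocation (*Trial design*). Treatment (2 levels) × setting (2 levels), so the interaction has 1 df (*Primary endpoint*).
- No imputation in the primary analyses (*Missing data*).

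**Assumptions, not stated in the article**
- f = d/2 = 0.22.
- d is in residual-SD units, i.e. after baseline adjustment.
- The two settings are of equal size, unless noted otherwise.

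**Method.** Noncentral F test with 1 numerator df, 4 cells and 1 covariate: denominator df = N − 5, noncentrality λ = N × f².

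**Step 1: the plan's own figure.** At N = 160, λ = 160 × 0.22² = 7.74 and power = 79.0%. The effect detectable with 80% power is f = 0.223, so d = 0.446. The stated 80% at d = 0.44 therefore reproduces to rounding with every randomised dyad evaluable.

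**Step 2: the planned evaluable sample.** At N = 128, λ = 128 × 0.22² = 6.20 and power = 69.5%. The effect detectable with 80% power is f = 0.250, so d = 0.50.

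**Step 3: what f = 0.22 means for treatment by setting.** In a balanced 2×2 layout, each cell's interaction deviation is ±f SD. The treatment effect in one setting is shifted by +2f and in the other by −2f, so the effects differ by 4f:
- f = 0.22 gives 4 × 0.22 = 0.88 SD, and 0.88 / 0.64 = 1.4 times the assumed overall effect.
- Detectable with 80% power at N = 160: 4 × 0.223 = 0.89 SD.
- Detectable with 80% power at N = 128: 4 × 0.2496 = 1.00 SD.

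**Step 4: if the settings' effects differ by 0.44 SD.** Then f = 0.44/4 = 0.11. At N = 128, λ = 1.55 and power = 23.5%. At N = 160, λ = 1.94 and power = 28.2%. Reaching 80% would take 651 evaluable dyads.

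**Step 5: unequal settings (the split is not given, so a range is assumed), N = 128**

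| Split | Power, 0.88 SD | Power, 0.44 SD |
|---|---|---|
| 50:50 | 69.5% | 23.5% |
| 40:60 | 67.7% | 22.7% |
| 30:70 | 61.9% | 20.5% |
| 20:80 | 50.6% | 16.7% |

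**Step 6: credit for the baseline covariate (r² is not given, so a range is assumed).** If differences are expressed in unadjusted SD, f is divided by √(1 − r²). At N = 128 with equal settings:

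| r² | Detectable difference, 80% power | Power, 0.88 SD | Power, 0.44 SD |
|---|---|---|---|
| 0 | 1.00 SD | 69.5% | 23.5% |
| 0.25 | 1.00 × √0.75 = 0.86 SD | 81% | 30% |
| 0.50 | 1.00 × √0.50 = 0.71 SD | 94% | 42% |

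Power for a 0.88 SD difference returns to 80% at r² = 1 − (0.22/0.2496)² = 0.22.

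**The case against.** The strongest reply is that nothing was miscalculated. The sentence refers to the sample size just named, 160, and the effect detectable there is d = 0.446. This stands: a reader might infer an arithmetic error, but the article's figure is right to rounding. The fault lies in the N chosen and in what d is taken to mean.

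A second reply is that the 70% gives no credit for the baseline covariate. If d is in unadjusted SD, r² of about 0.22 restores 80% power at 128 dyads. This stands in part. The article states neither the scale nor the correlation, so the 70% is conditional. The rescue applies only to a 0.88 SD difference, however; a 0.44 SD difference still has no more than 42% power at r² = 0.5.

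Third, the article never says that d = 0.44 is the difference between inpatient and outpatient effects, and it names other moderators too. That is correct, and it is why the label should be called misleading rather than the power false on this ground. The 0.88 SD conversion holds for a balanced two-level moderator.

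Fourth, the moderator analyses are exploratory, the sample size was derived from the main effect, and *Aims and hypotheses* contains no hypothesis of a setting difference. All of this stands and limits the weight of the point. It does not excuse a stated power that the planned evaluable sample does not deliver on the basis on which it reproduces.

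**Conclusion.** The point holds as a minor-to-moderate correction of a stated figure. On the reading that reproduces it (f = d/2, residual-SD units), the 80% requires zero drop-out. After the article's own 20% attrition, power is about 70% and the detectable effect is d = 0.50. For treatment by setting with equal-sized settings, the effect quoted as moderate is a 0.88 SD difference between settings, larger than the whole assumed effect of 0.64. A 0.44 SD difference has about 23% power at 128 dyads and 28% at 160, and less if the settings are unequal.

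Two stronger readings are not supported. One is that the trial's primary power or sample size is undermined: neither depends on this sentence. The other is that the investigators will treat a non-significant interaction as proof of equal efficacy: the article nowhere says so. The wording only leaves room for that inference.

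**What to change.** Replace the moderator sentence under *Sample size considerations* with wording such as:

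> With 128 evaluable dyads and equal-sized settings, a difference between settings in treatment effect of about 1.0 residual SD is detectable with 80% power; power for a difference of 0.44 residual SD is about 23%, and lower if the settings are unequal in size.

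If credit is taken for the baseline covariate, state the assumed correlation and apply it to both figures. At an assumed r² of 0.25 to 0.5, for example, the detectable difference is 0.86 to 0.71 SD and power for 0.44 SD is 30% to 42%. Adjusted and unadjusted figures should not be mixed in one statement.

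Add one line saying that a non-significant interaction is not evidence of equal efficacy across settings.

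The cost is one rewritten sentence, one added line and a less favourable stated figure. Recruitment, conduct and the primary analysis do not change.

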### Data analyses

#### General considerations and socio-demographic data

Socio-demographic and clinical information are described at baseline using frequencies and percentages (e.g. categorical variables) or means and standard deviations (e.g. continuous variables), and treatment conditions compared to assess potential baseline differences. The statistical analyses are based on all mother-child dyads included in the study after randomisation (Fig. 1), according to ITT (Intention to Treat) principles. The data to be used in all analyses (unless otherwise stated) is defined as the Full Analysis Set (FAS) and includes all mother-child dyads after randomisation, irrespective of the treatment received. Data from mother-child dyads who drop out of the study are included in the FAS up to the date they withdraw. The Per Protocol (PP) population is a subset of the FAS and includes mother-child dyads who conform to the study plan (i.e. sufficient treatment adherence, no major protocol violations). The safety population is defined as mother-child dyads who have participated in at least one intervention session, and is analysed according to the treatment they received.

#### Primary endpoint

The primary analysis of the primary endpoint (maternal sensitivity measured using the EAS subscale after 6 weeks) will be analysed using ANCOVA based on the FAS population using PIP versus CAU as the factor treatment group, EAS sensitivity at baseline as covariate, and the stratification variable treatment setting. Results will be displayed as adjusted means of the treatment group together with 95% confidence intervals and the respective *p* value (two-sided). The significance level is set at α =0.05. All further analysis is considered exploratory.

A secondary analysis of the primary endpoint will also be carried out using the ANCOVA model based on the PP population. Additional moderator analyses of the efficacy of PIP for a change in maternal sensitivity (EAS) will be conducted with treatment setting as the moderator, i.e. by additionally adding a ‘treatment group’ * ‘treatment setting’ interaction term to the model. Further moderator analyses regarding the efficacy of PIP will comprise maternal attachment type (AAI attachment) or maternal reflective functioning (AAI RF) as moderators.

In addition, models incorporating multiple imputation methods based on the PP population and a hierarchical regression model (including the therapist as a grouping factor and therapist’s adherence as covariate) will be used for sensitivity analyses of the primary outcome. To investigate the longitudinal change of the primary endpoint, linear mixed models (LMMs) incorporating both measurement points for each outcome (FAS population) will be computed. To explore further effects of additional predictors (such as the therapists carrying out the interventions), the models will be compared based on model fit values (AIC, the Akaike Information Criterion), with these predictors included in the model term.

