#### Secondary endpoints

Primary analyses of the secondary endpoints replicate the computation of the models for the primary endpoint, as either ANCOVAs or logistic regressions (depending on the continuous or dichotomous scale of the respective endpoint). Group differences in the children’s attachment organisation (SSP/ AQS, binarised evaluation: secure/ insecure attachment), as well as all responder analyses (EAS sensitivity, EPDS, PRFQ, PSI at T1 and T2; SFS at T1, CBCL at T1 and T2), will be computed as logistic regressions adjusted for the stratification variable treatment setting with presentation of odds ratios. Should no cut-off values be available, dichotomous response variables for these measures will be computed using the Reliable Change Index (RCI; RCI > 1.96) [45]. Linear mixed models will be used to analyse the change in the secondary endpoints (maternal stress level, reflective functioning (PRFQ), and infantile symptoms) during the course of the study (12-months follow-up) across all measurement points.

Additional sensitivity analyses will be performed for health economic parameters as secondary endpoints, varying unit-cost assumptions for documented health care utilisation within realistic ranges. All secondary analyses of the primary and secondary endpoints are considered exploratory.

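### Randomisation is stratified by setting and study centre, but the primary ANCOVA adjusts only for setting; if centre is prognostic, the test is conservative and loses a little power

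*Protocol article*

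**What the plan says.** Under Trial design, the protocol article describes allocation as "applying a 1:1 block randomisation with variable block length and stratified by setting (inpatient/outpatient) and study centre". The trial "is currently underway in Leipzig, Berlin, Potsdam and Hamburg", so four locations are named.

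Under Primary endpoint, the ANCOVA for 6-week EAS sensitivity has three terms: treatment group, "EAS sensitivity at baseline as covariate, and the stratification variable treatment setting". Setting appears as if it were the only stratification variable. All further analysis is declared exploratory, so this is the one confirmatory model.

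Under Secondary endpoints, the main analyses repeat the primary model, and the logistic regressions are "adjusted for the stratification variable treatment setting with presentation of odds ratios".

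No analysis in the article names centre as a covariate, stratum or random effect. The hierarchical model under Primary endpoint groups by therapist and is a sensitivity analysis. The AIC comparison of further predictors is exploratory.

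**The concern.** Stratified blocks keep the arms balanced within each centre, so differences between centres largely cancel out of the PIP minus CAU contrast. A model without centre does not know this. It counts the between-centre variance as noise and reports a standard error larger than the true sampling variability of the estimate. The confidence interval is then wider than it need be, the test rejects less often than its nominal 5% under the null, and some of the precision that stratification offered is not used.

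The planned sample was reduced from 180 to 160 dyads because of recruitment and funding limits, so precision that costs almost nothing is worth keeping. The covariate set should also be settled before unblinding, because adding centre afterwards would invite doubt about the primary result.

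**Working it through.** **Inputs from the protocol article.** Two-sided α = 0.05; d = 0.64; 64 per group after drop-out; 20% drop-out; N = 160; primary analysis without imputation. Analysed sample: 160 × 0.8 = 128, or 64 per group.

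**The plan's own figure.** The drop-out step reproduces: 64 / 0.8 = 80 per group. The 64 does not reproduce as the number needed for 90% power. A two-arm, 1-df comparison at d = 0.64 needs 53 per group for 90%, and 64 per group gives about 95%. That is a separate matter. Here it means only that the starting power is about 95%.

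**Assumption.** Let ρ be the share of the variance remaining after baseline EAS and setting that is due to centre. The documents give no value, so ρ is varied from 0 to 0.20. Treatment is taken as balanced within centre, and d is expressed in units of the SD that remains after baseline and setting.

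**Formulas** (n = 64 per group, SD = 1):

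- SE reported without centre: √(2/n) = √(2/64) = 0.177.
- True SE under stratification: √((1 − ρ) × 2/n).
- Ratio of the two: k = 1/√(1 − ρ).
- Residual df: 128 − 4 = 124 without centre and 121 with four centres (3 more terms). The critical value is 1.98 in both cases.
- Type I error without centre: 2 × (1 − Φ(1.98 k)).
- Noncentrality: δ = d √(n/2), which is 3.62 at d = 0.64 and 2.83 at d = 0.50.
- Power without centre: Φ((δ − 1.98) k). Power with centre: noncentral t with noncentrality δk and 121 df.

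**Example, ρ = 0.20.** k = 1/√0.8 = 1.118. Type I error: 2 × (1 − Φ(2.21)) = 0.027. Power without centre at d = 0.64: Φ(1.64 × 1.118) = Φ(1.83) = 96.7%.

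| ρ | SE too wide by | Type I error without centre | Power at d = 0.64, without → with centre | Power at d = 0.50, without → with centre |
|---|---|---|---|---|
| 0 | 0% | about 5% | 95.0% → 94.9% | 80.2% → 80.1% |
| 0.05 | 2.6% | 4.2% | 95.4% → 95.8% | 80.8% → 82.1% |
| 0.10 | 5.4% | 3.7% | 95.8% → 96.6% | 81.5% → 84.1% |
| 0.20 | 11.8% | 2.7% | 96.7% → 98.0% | 82.9% → 88.0% |

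At ρ = 0 the type I formula returns 4.8%, because it ignores the sampling variation of the estimated SE; the exact value is 5%. The other entries in that column are therefore slightly low.

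**Simulation check** (4000 runs per scenario, 128 dyads, four equal centres). At ρ = 0.10 the mean model SE is 0.177 without centre and 0.168 with it. Rejection under the null is 3.6% without and 4.8% with. Power is 95.0% and 96.3% at d = 0.64, and 80.6% and 83.3% at d = 0.50. At ρ = 0.20, rejection under the null is 2.5% without centre and 4.9% with it.

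**The case against.** The strongest reply is that the loss is conditional and small. It arises only if centre is prognostic once baseline EAS and setting are in the model, and nothing in the article shows that it is. At the planning effect, power stays above 90% either way, and the error is on the safe side. All of this stands, and it limits the weight of the point. It does not explain why a factor used to randomise is missing from a model whose terms are listed explicitly. Condensing a protocol into an article does not explain it either, because the model is stated, not omitted.

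Some stronger readings are tempting but not supported:

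- A reader might infer that the centres differ in case mix and in the content of CAU, so that centre must matter. The article describes neither by centre. It ties differences in CAU intensity to inpatient versus outpatient care, which the model already contains. It also describes one PIP manual with common training, and outcome coders blind to allocation. Different therapists are plausible, and the therapist-level sensitivity model covers part of that, but not in the primary analysis.
- A reader might turn a 5 to 15% centre share into 8 to 24 of 160 dyads thrown away. About 128 dyads are analysed, so the count would be 6 to 19 (0.05 × 128 to 0.15 × 128), and even that describes nominal interval width. In terms of power the equivalent is smaller: roughly 4 to 13 of 128 at d = 0.50, and somewhat fewer at d = 0.64.
- A reader might carry the precision argument over to the logistic models. It does not transfer. Adding a prognostic covariate there changes the conditional odds ratio and does not shrink its standard error.

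**Conclusion.** The mismatch between the randomisation and the primary model is certain from the text. Its consequence is conditional. If centre explains 0 to 20% of the residual variance, with about 128 dyads and balance within centre, the standard error is 0 to 12% too wide and the true type I error runs from about 5% down to 2.7%. The power lost is about 0 to 1.3 points at d = 0.64 and 0 to 5 points at d = 0.50. With no centre effect, nothing is lost.

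A reader might take the omission as a threat to the validity of the primary result. It is not: the treatment estimate stays unbiased and false positives become rarer, not more frequent. This is a modest matter of efficiency and calibration, worth correcting because the correction is nearly free.

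**What to change.** Add study centre, coded as in the randomisation, to the primary ANCOVA alongside treatment group, baseline EAS sensitivity and setting. Do the same in the secondary ANCOVAs that repeat this model. The article names four cities and also refers to participating clinics in them, so the number of centre strata is not certain. If there are more than four, or some are small, prespecify a pooling rule or a random centre effect. If centre is left out on purpose, state the reason.

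The cost is a change of wording before unblinding and, with four centres, 3 degrees of freedom out of about 120. If centre proves unrelated to the outcome, the power given up is about 0.1 point.
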